### Implementation, feasibility, and adaptation

We will examine changes across time of feasibility, acceptability, adoption, and sustainment for both interventions. The Proc Mixed random intercepts multi-level repeated measures model will be used where variations in changes are estimated and the effects of time, study arm (PN vs. MHU), and their interaction will be tested as fixed effects. Baseline measures of each dependent measure will be used in the analyses as covariates.

Convergence of the data will bolster validity in the findings by merging qualitative and quantitative data to provide insight into the effectiveness of the interventions. This is especially important to promote validity for implementation science studies that typically use nested designs with a small sample of communities [73]. We will (1) assess intra-cluster (community) correlations (all conditions); (2) summarize (descriptive stats) individual and community characteristics for each intervention arm (numbers analyzed, the average cluster size, cluster characteristics, and important staff/client characteristics). If differences exist between conditions, the variables will be included as selected covariates in analytic models. An intention-to-treat approach will be used whereby observations are analyzed in their intended condition. Also, protocol implementation measures will be recorded, summarized, and reviewed monthly in order to inform real-time adjustments (e.g., changes in protocols if adherence to the protocol is not met). At project end, difference in proportions will be calculated as a measure of effect, and large-sample 95% confidence limits calculated as a measure of precision.

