## Interventions

### Patient navigation (PN) arm

Our PNs will be individuals that ideally have “shared living experiences” (e.g., HIV or history of SUD treatment) with participants and will help them overcome barriers to accessing and engaging in quality care [15]. We will work with our community partners to assure that our PNs are integrated as members of the community health care teams. The PN will work closely with the study participants to access medication for opioid use disorders, behavioral health for stimulant use and other SUDs, HIV and HCV testing, prevention, and treatment, as well as other primary health care. They will also assist with housing, health insurance, transportation, childcare, and other needs during the six-month intervention. Across all four community sites, ACTION PNs will receive active, comprehensive training and guidance on providing appropriate linkage to community services including harm reduction services such as syringe services programs in Connecticut (not available in Texas) and education on safe injection practices of substances to reduce HIV and HCV infection and reinfection.

The community partners collaborating on this project have extensive experience in PN support services, their PN protocols will provide a guiding framework for the ACTION training protocol. PN training will capitalize on existing linkages to an array of services through Federally Qualified Health Centers or similar organizations, including primary care, substance use treatment, behavioral health, case management, and care coordination. In addition, these services include confidential rapid HIV and HCV testing, education about prevention of HIV and HCV care, PrEP, post-exposure prophylaxis for HIV, and MOUD (buprenorphine and extended-release naltrexone). All PNs will be trained to provide motivational interviewing and goal setting as part of their services provided in the project as it has been shown to improve treatment engagement in persons who use substances [63, 64].

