### Mobile health unit (MHU) arm

MHUs in the four project areas will either operate and provide care directly on the MHU. All MHUs will provide on-site integrated HIV, HCV, and substance use testing, prevention, diagnosis, treatment, and care. When medications are not able to be provided on the MHU, a clinician on the MHU (or via referral) will provide prescriptions for any medications related to their care, including MOUD (buprenorphine/naltrexone and extended-release naltrexone). Furthermore, the MHU team will have an established relationship with Ryan White Qualified Healthcare programs and other community organizations for linkage to services in the community they are not able to provide directly. A community health worker (CHW) will be on the MHU and will assist in referring and linking participants to community-based services as needed.

Prior to the end of the six-month intervention period, study staff will work to transition participants randomized to the MHU arm to either another MHU that is convenient to them or other community-based services in order to maintain continuity of care. Protocols have been developed in each of the communities in Connecticut and Texas to identify community locations in which to locate the MHUs that will be accessible by the target populations.

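### For the implementation outcomes, covariates are chosen by observed arm differences from a list that includes staff traits, which can adjust away part of the PN-versus-MHU effect

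*Protocol article*

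**What the plan says.** All of this is in the protocol article.

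- **Outcomes covered** (Implementation, feasibility, and adaptation): "We will examine changes across time of feasibility, acceptability, adoption, and sustainment for both interventions".
- **Model** (same section): a random-intercepts repeated-measures model in which "the effects of time, study arm (PN vs. MHU), and their interaction will be tested as fixed effects". The baseline value of each dependent measure is a covariate.
- **Summaries by arm** (same section): "numbers analyzed, the average cluster size, cluster characteristics, and important staff/client characteristics".
- **Covariate rule** (the next sentence): "If differences exist between conditions, the variables will be included as selected covariates in analytic models". The paragraph then commits to intention-to-treat. It ends with a difference in proportions and large-sample 95% limits at project end.
- **Allocation** (Study design and settings; Randomization): individual participants, 1:1, stratified by project site. Both arms therefore run in every community.
- **Staffing, PN arm** (Patient navigation (PN) arm): "Our PNs will be individuals that ideally have “shared living experiences” (e.g., HIV or history of SUD treatment) with participants".
- **Staffing, MHU arm** (Mobile health unit (MHU) arm): "a clinician on the MHU (or via referral) will provide prescriptions", and a community health worker on the unit handles referral and linkage. The Background also counts the cultural competence of staff among the features of the MHU approach.

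**The concern.** The only selection criterion printed is an observed difference between arms, and staff characteristics are on the list it draws from. Nothing exempts staff variables or anything else determined after randomisation.

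A baseline client variable that differs by chance is harmless to adjust for, although choosing it on imbalance rather than prognostic value is weak practice. A staff trait that differs because the arms are staffed differently is another matter: it is part of what participants were randomised to receive. Conditioning on it changes the question from PN versus MHU as delivered to PN versus MHU with staffing held equal. That fits poorly with the intention-to-treat statement in the same paragraph.

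At stake are the arm comparisons for feasibility, acceptability, adoption and sustainment. Feasibility and acceptability make up the trial's secondary aim.

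**Working it through.** **No figure to reproduce.** The protocol states no sample size, power or alpha for the implementation models.

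**Step 1. What the rule can pick up in this design.**

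- *Community characteristics*: both arms run at every site, so there is no systematic arm difference.
- *Client characteristics at baseline*: individual randomisation, so differences arise by chance only.
- *Numbers analysed and average cluster size*: arm-level summaries, not usable as participant-level covariates.
- *Staff characteristics*: can differ systematically, because the intervention sections staff the two arms differently.

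The one listed class that can differ systematically is thus the class that should stay out of a model estimating the arm effect.

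**Step 2. Effect on the arm coefficient.** Let A be arm (MHU = 1) and S a binary staff trait attached to the participant, with prevalence p_PN and p_MHU. Let the outcome be direct × A + staff × S + error, with residual SD 1.

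- Without S, the arm coefficient = direct + staff × (p_MHU − p_PN), the total effect.
- With S, the arm coefficient = direct only.
- With equal arms, corr(A, S) = r = 0.5 × (p_MHU − p_PN) / √[p̄(1 − p̄)], where p̄ is the mean of the two prevalences. The standard error is multiplied by 1/√(1 − r²).

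**Step 3. Illustration.** N = 689 is the 6-month figure from Sample size and power calculations, which relates to the time-to-initiation outcome and is borrowed here. The prevalences, direct effect (0.10 SD) and staff effect (0.20 SD) are assumptions.

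Worked case, 20% PN and 80% MHU:

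- Total effect = 0.10 + 0.20 × 0.60 = 0.22.
- r = 0.5 × 0.60 / √0.25 = 0.60, so the multiplier is 1/√(1 − 0.36) = 1.25.
- SE = 2/√689 = 0.076 without S, and 0.076 × 1.25 = 0.095 with S.

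A simulation of 2,000 replicates per row agrees:

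| Trait prevalence PN/MHU | r | SE multiplier | Estimate without → with S | SE without → with S | Rejection rate without → with S |
|---|---|---|---|---|---|
| 50/50% | 0 | 1.00 | 0.10 → 0.10 | 0.077 → 0.076 | 26% → 26% |
| 20/50% | 0.31 | 1.05 | 0.16 → 0.10 | 0.077 → 0.080 | 56% → 24% |
| 20/80% | 0.60 | 1.25 | 0.22 → 0.10 | 0.076 → 0.095 | 81% → 19% |
| 5/95% | 0.90 | 2.29 | 0.28 → 0.10 | 0.076 → 0.177 | 96% → 10% |

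**Step 4. Staff trait with no effect on the outcome.** With a direct effect of 0.20 SD and a staff effect of zero, the estimate stays at about 0.20 in every row, so there is no bias. At 5/95% the rejection rate still falls from 74% to 22% through collinearity. At 0/100%, r = 1 and the arm effect cannot be estimated.

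The distortion vanishes in the 50/50% row and grows with the arm difference in S, and that difference is what triggers the rule.

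**The case against.** The case on the other side has real force.

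- **Discretion.** The text speaks of *selected* covariates. A reader might infer that every variable that differs must be entered, but the wording does not go that far. What stands is that no other criterion is stated.
- **Arm-level counts.** A reader might also infer that the analyst must adjust for numbers analysed or cluster size. Each is a summary with one value per arm, so this is not a credible reading, and the point does not rest on it.
- **Staff may not differ on what is measured.** Lived experience is only an ideal for navigators, the community health worker's role overlaps with navigation, and the article does not say which staff traits would be recorded. *Staff* might even mean agency respondents. These are fair limits: a difference is possible, not certain. The staff delivering the arms still fall within the wording.
- **Another effect measure.** The end-of-project difference in proportions is described without covariates. A reader might infer that a true difference would be reported as none, but this contrast could still show it.
- **Numbers.** No prevalence, effect size or significance screen for imbalance is given. Any power loss, or any false-imbalance rate from testing many variables at 5%, therefore describes assumptions and not this plan.
- **Client covariates.** Adjusting for a chance baseline imbalance does not remove a treatment effect. For client variables the issue is pre-specification only.

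**Conclusion.** The point holds for the implementation outcomes. A printed rule selects covariates by observed arm difference from a list that names staff characteristics, for models that test study arm in an individually randomised trial. Where a staff trait differs because of how the arms are staffed, entering it can remove part of the PN-versus-MHU effect, inflate its standard error, or both.

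The mechanism follows from the design. The size does not: it depends on which traits are measured, how far they separate the arms and how much they affect the outcome. Under the assumptions shown, the effect ranges from none (trait balanced) to an estimate reduced from 0.28 to 0.10 SD with a standard error 2.29 times as large (5/95% split). If staff traits do not affect the outcome, the loss is of precision only.

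A reader might extend this to the primary outcome. The document does not support that: the rule sits in the implementation section, and the primary Cox model is described separately as adjusted for relevant covariates, without an imbalance trigger. The wording should be changed before these outcomes are analysed; the trial's main comparison is not in question.

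**What to change.** Replace the imbalance-triggered sentence with a statement on these lines: models comparing PN with MHU on implementation outcomes adjust for site, the baseline value of the outcome and a short pre-specified list of prognostic participant covariates measured before randomisation, whatever imbalance is seen. Add that staff characteristics are reported descriptively by arm, or examined in a separate exploratory mediation analysis, and are not entered in models estimating the arm effect.

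The cost is one or two sentences and no new data. The baseline outcome is already a planned covariate, and site is already the stratification factor. The small downside is that a chance imbalance in an unlisted baseline variable would be handled only in a sensitivity analysis.

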### Cost effectiveness

Cost analysis will be conducted to estimate costs of the PN and MHU interventions using established micro-costing methods to identify, measure, and value all resources for the implementation of both interventions. We will estimate costs for the PN and MHU study sites including start-up costs (e.g., staff training, equipment purchases); variable costs (e.g., labor time for staff providing services to clients); time-dependent costs (e.g., record-keeping, vehicle operating costs); and overhead costs. Costing data will be collected by using site records on numbers of services provided to clients, estimates of the time required to provide services obtained through staff interviews, and site financial records. Costs will be calculated by applying national labor rates (to improve generalizability) to staff time estimates or obtaining direct costs of equipment from financial records. Results will be reported as annual costs for each of the arms in total, by cost component (i.e., start-up, ongoing costs, overhead), and per client served. To determine additional healthcare system and societal costs from PN and MHU use, we will use self-reported data on the use of medical and substance use treatment services, criminal activity, and engagement with the justice system outside of the study interventions. This data will be collected from participants in the baseline and follow-up assessments. We will use Medicare fee-for-service payment estimates to approximate healthcare system costs incurred by providers. Differences in levels of health service utilization will be estimated to determine the impact of different interventions on costs to the healthcare system 6 and 12 months after baseline.

All cost analyses will be conducted using a multivariable generalized linear mixed model (GLMM). The GLMM is an extension of the generalized linear model that allows for the inclusion of random effects for each study site. Separate multivariable GLMM will be estimated to predict the mean value for each resource and outcome, at each time period, by model (PN and MHU), and participating community. To account for sampling uncertainty in point estimates, the p-values and standard errors will be estimated using nonparametric bootstrapping techniques. Discounting for time preference will not be required since measures will not be obtained beyond 12 months after the baseline interview.

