## Methods

### Study design and settings

ACTION (Addressing risk through Community Treatment for Infectious disease and Opioid use disorder Now) is a five-year hybrid type 1 effectiveness-implementation randomized control trial which compares noninferiority of two models of linking justice-involved individuals to the continuum of community-based HIV and SUD prevention and treatment service cascades of care funded by the National Institute on Drug Abuse. Adults with a history of opioid and/or stimulant use who are currently incarcerated or were involved with the justice system within the past 30 days will be recruited across two Connecticut communities (New London and Windham/Tolland/Middlesex Counties) and two Texas communities (Dallas and Tarrant Counties). A total of 864 participants will be enrolled in the project, 216 from each of the four project sites. Participants will be randomized 1:1 to one of two models of care: (1) a PN for linkage to care, or (2) services delivered via a MHU for a six-month intervention period in each model. For the PN arm of the study, the navigators will assist in linking study participants to appropriate community service providers. Services include SUD treatment, including MOUD, and HCV testing and treatment. PLH will receive assistance with gaining initial or continued access to antiretroviral therapy (ART) services, and those at risk for HIV will be provided access to PrEP services. For those randomized to the MHU arm of the study, these clinical services will be provided along with the assistance of a community health worker (CHW) on board the MHU. When possible, participants will receive PrEP/ART services and prescriptions, SUD screening and diagnoses, MOUD prescription, and harm reductions services on the MHU. If a service cannot be provided directly on the MHU, participants will be linked to the appropriate community-based service providers. This study is multi-site collaboration with Yale University, the University of Texas Southwestern, and Texas Christian University, along with their community and justice system partners. The study has been funded from September of 2020 through August of 2025.

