### Healthcare initiation, adherence, and retention of care

Data will be collected to create treatment cascades associated with HIV, PrEP, HCV, MOUD, and STI testing, diagnoses, treatment, and care. Diagnoses and sero-conversion of HIV, HCV, and STIs will be assessed through medical history at every visit and via biological tests noted below. Based on diagnoses and current medications, time to linkage, initiation, or continuation of ART, PrEP, HCV, MOUD, or STI care and medications will be assessed from time of release from justice-based facilities, after randomization for those in the community, or upon diagnosis throughout the 12-month study participation period. Adherence to ART, PrEP, HCV, and STI treatments will be assessed using a visual analog scale (VAS [50]) for daily medications. Biological measures described below will assist with the evaluation of ART and PrEP adherence. For PLH at time of randomization the percent who maintain or achieve HIV viral load < 200 copies/mL at 6 months [51, 52] will be collected. Persistence on medication will be determined by assessing if medication was discontinued and reason for discontinuation, including successful cure of the infection if applicable. Attendance to medical visits will be confirmed with community providers and the MHU.

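### The costing boundary puts MHU clinical care inside the intervention and the equivalent PN community care outside it, so neither cost stream alone, nor an unharmonised sum, compares the arms like for like

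*Protocol article*

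**What the plan says.** The Cost effectiveness section of the protocol article sets up two cost streams.

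- **Intervention costs.** These are estimated "using established micro-costing methods to identify, measure, and value all resources for the implementation of both interventions". On the source, "Costing data will be collected by using site records on numbers of services provided to clients", supplemented by staff interviews and site financial records. Staff time is priced at national labor rates. The components include "variable costs (e.g., labor time for staff providing services to clients", together with vehicle running costs and overhead. Results are reported per year and per client for each arm.
- **Wider healthcare and societal costs.** These rest on self-reported "data on the use of medical and substance use treatment services, criminal activity, and engagement with the justice system outside of the study interventions". For pricing, "We will use Medicare fee-for-service payment estimates to approximate healthcare system costs incurred by providers". Differences between arms in service use are then to show each intervention's effect on healthcare-system costs at 6 and 12 months.

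The arms place clinical care differently. Under Mobile health unit (MHU) arm, "All MHUs will provide on-site integrated HIV, HCV, and substance use testing, prevention, diagnosis, treatment, and care". For PN, Study design and settings says that "the navigators will assist in linking study participants to appropriate community service providers". The same section adds that MHU services are given on board when possible and otherwise referred to community providers.

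Under Healthcare initiation, adherence, and retention of care, the article also states: "Attendance to medical visits will be confirmed with community providers and the MHU".

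**The concern.** The boundary between the streams is the intervention itself, and the two interventions contain different things. A PrEP visit on the unit is part of the MHU intervention, so it is counted from site records and micro-costed. The same visit by a PN participant takes place at a community clinic, outside the intervention, so it is self-reported and priced at Medicare rates. On-board care replaces community care, which means that the measurement method is tied to the assigned arm for exactly the services the trial is meant to move.

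Two consequences follow for the planned outputs. The per-client intervention cost contains clinical care for MHU but mainly navigation for PN. The comparison of service use leaves out on-board visits, so MHU could appear to save healthcare resources only because care moved onto the unit. Adding the streams removes the omission but leaves a different source of quantities and a different price basis. Randomisation, the mixed models and bootstrapping do not correct measurement that differs by arm.

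**Working it through.** The article states no unit cost or cost difference, so there is no figure to reproduce. The check traces one clinical service through the stated rules and then shows what the rules imply under assumed values.

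**Tracing one PrEP or MOUD visit**

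| Where it takes place | Relative to the intervention | Quantity from | Price basis |
|---|---|---|---|
| On the unit (MHU arm) | inside | site records | micro-cost |
| Community provider (PN arm) | outside | self-report | Medicare |
| Community provider after MHU referral | outside | self-report | Medicare |

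**Inputs (all assumed; the article gives none)**

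- True clinical use and true cost are equal in both arms, at 100 per participant.
- s = share of MHU-arm clinical care given on board, 0.5 to 1.0.
- r = self-reported use divided by true use, 0.8 to 1.0.
- m = Medicare price divided by micro-cost, 0.7 to 1.3.

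**Service-use comparison alone.** PN records a share r of true use and MHU records r(1 - s). The apparent relative reduction for MHU is [r - r(1 - s)]/r = s. With s between 0.5 and 1.0, MHU seems to use 50% to 100% less of these services although true use is equal.

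**Sum of the two streams**

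- MHU = 100 × [s + (1 - s) × r × m]
- PN = 100 × r × m
- MHU minus PN = 100 × s × (1 - r × m)

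| s | r | m | MHU | PN | Difference |
|---|---|---|---|---|---|
| 1.0 | 0.8 | 0.7 | 100.0 | 56.0 | +44.0 |
| 0.8 | 0.8 | 0.7 | 91.2 | 56.0 | +35.2 |
| 0.8 | 0.8 | 1.0 | 96.0 | 80.0 | +16.0 |
| 0.8 | 1.0 | 1.0 | 100.0 | 100.0 | 0.0 |
| 0.8 | 1.0 | 1.3 | 106.0 | 130.0 | -24.0 |
| 1.0 | 1.0 | 1.3 | 100.0 | 130.0 | -30.0 |

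The difference vanishes only when r × m = 1.

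**Alternative reading of the boundary.** The phrase about services outside the interventions might qualify only justice-system engagement. Self-reported on-board visits would then also be Medicare-priced, on top of their micro-cost. MHU becomes 100 × (s + r × m), PN stays at 100 × r × m, and the excess from double counting is 100 × s, or +50 to +100 over the same range of s. The service-use comparison would no longer omit on-board visits, but the total would still not be comparable.

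**Effect of the fix.** Counting visits equally well in both arms sets r = 1, which leaves 100 × s × (1 - m). At s = 0.8 this is +24 at m = 0.7 and -24 at m = 1.3. Using one price basis as well sets m = 1, and the difference is 0 for every s.

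**The case against.** The case on the other side has several sound parts.

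- **The text does not assign methods by arm.** A reader might infer that MHU is micro-costed and PN is self-reported. Both methods apply in both arms: navigators' time is micro-costed, and MHU-arm care referred off the unit is self-reported and Medicare-priced. The asymmetry follows from what each intervention contains and is limited to on-board services.
- **A primary outcome might seem to be compromised.** The cost item among the primary implementation outcomes (Abstract; Feasibility and acceptability procedures) is what it takes to implement, sustain and scale up the approaches. That is programme cost, and it is micro-costed in both arms. Cost offsets are listed under additional aims.
- **Dropout might seem to widen the gap.** The sample size section expects 80% retention at 6 months, but assessments also take place at months 1 and 3, and a model fitted to observed data does not treat missing follow-up as zero cost. The article does not support reading r = 0.8 as the effect of 20% loss.
- **Direction might seem clear.** Every input above is assumed and the range crosses zero, so the article does not show that MHU would look dearer or cheaper in total.
- **The article condenses a fuller plan.** It prints no rule for combining the streams, and such a rule may exist elsewhere. Its absence is not criticised here.
- **Common pricing has a price.** The Background presents possible savings from mobile delivery as part of the rationale, and one tariff for every setting would erase a true unit-cost difference.

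Micro-costing a new programme and using tariffs for other care is also common practice. That works when the other care is a similar background in both arms. Here the on-board care replaces it, so the core of the point stands.

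**Conclusion.** The point holds within limits. As the boundary is stated, intervention cost per client and outside service use each give an unlike comparison of the arms, and their sum is open to differential measurement. With equal true cost of 100 per participant, the illustrative artefact runs from +44 to -30 over the assumed ranges. These figures show what the rules allow and do not estimate the bias in this trial. The conclusion rests on reading the boundary as applying to medical and substance use services; the alternative reading exchanges omission for possible double counting.

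The scope is the cost-offset and healthcare-system comparison. The micro-costed programme cost stands as a description of what each model costs to run, and the time-to-initiation analysis is untouched. It is an inexpensive correction worth making before costs are compared.

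**What to change.** For the between-arm comparison of healthcare use and total cost:

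1. Count HIV/PrEP, HCV and SUD services in both arms wherever they are delivered. Use MHU records for on-board care. For community care, use the attendance confirmed with providers, the prescription receipt covered by medical releases (Post enrollment) and the PrEP/ART pharmacy fill dates (HIV, HCV, and OUD cascades of care). Self-report is the fallback, and each visit is counted once.
2. Keep micro-costing as the programme-cost result, labelled as such. Base arm comparisons on the combined total and not on either stream alone.
3. Add a sensitivity analysis that prices the shared clinical services on one common basis in both arms.

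The cost is some wording and the work of mapping on-board services to common prices; no new visits are needed. Provider confirmation will be incomplete where no release is signed, and fill dates are described only for PrEP and ART, so self-report will still carry part of the community count. Common pricing hides any true unit-cost difference of mobile delivery, which is why it should remain a sensitivity analysis.
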